## Abstract

The Collaborative Approach to Reach Everyone with Familial Hypercholesterolemia (CARE-FH) study aims to improve diagnostic evaluation rates for FH at Geisinger, an integrated health delivery system. This clinical trial relies upon implementation science to transition the initial evaluation for FH into primary care, attempting to identify individuals prior to the onset of atherosclerotic cardiovascular disease events. The protocol for the CARE-FH study of this paper is available online. The first phase of the project focuses on trial design, including the development of implementation strategies to deploy evidence-based guidelines. The second phase will study the intervention, rolled out regionally to internal medicine, community medicine, and pediatric care clinicians using a stepped-wedge design, and analyzing data on diagnostic evaluation rates, and implementation, service, and health outcomes.

## 1. Introduction

Familial hypercholesterolemia (FH) is a hereditary cause of high cholesterol that leads to premature cardiovascular disease. Despite evidence-based guidelines for diagnosis and treatment, FH remains under-diagnosed and under-treated [1,2,3,4]. Individuals with a pathogenic genetic variant in an FH gene have triple the risk for atherosclerotic cardiovascular disease (ASCVD) compared with those without a variant at any low-density lipoprotein-cholesterol (LDL-C) level, presumably due to lifelong exposure to elevated LDL-C levels. The diagnosis of FH is often made in middle-aged adults, after experiencing premature ASCVD [5]. Event rates for an FH patient with prevalent ASCVD are 5-fold higher compared to those with no prior ASCVD [6]. Treatment beginning in adolescence lowers the risk for ASCVD before the age of 40 years from about 25% to <1% [3,7]. Diagnostic tools and effective medications to lower LDL-C exist. Prevention of ASCVD has been proven to be cost-effective. The care gap created by the lack of FH diagnosis is large.

Published focus groups conducted with individuals with FH and clinicians have found information technology (IT)-based algorithms to identify FH to be acceptable, appropriate, and feasible [8]. However, barriers exist to referring potential individuals with FH for clinical care including unfamiliarity of patients and non-specialty clinicians with the importance of an FH diagnosis, lack of experience with IT-based diagnostic strategies, concerns about genetic discrimination, psychological consequences related to a genetic diagnosis, gender/race/ethnicity, and time/cost burden [9]. IT-based strategies currently in use, and proposed, identify a large number of patients (1–2% of all patients in a given cohort) needing evaluation—more than can be accommodated into existing lipid specialty clinics [10,11,12]. Though FH care in an uncomplicated patient without ASCVD is relatively straightforward, (i.e., start a statin, monitor LDL-C levels, assess for side effects), lack of awareness among primary care clinicians regarding FH and discomfort with starting lipid lowering therapy in younger patients has contributed to this observed care gap. Primary care clinicians will need enhanced management skills and systems to successfully manage the projected caseload.

Implementation strategies can be used to improve the uptake of evidence-based guideline care for FH. Implementation science has been used to create a care delivery model that facilitates the relaying of genetic diagnostic information to at-risk patients [13]. Processes for returning genetic results for many disease-causing genes are in place, but this remains a work in progress given the diversity and complexity of the information related to the many diseases covered by the program. For FH, complicating factors are: explaining ASCVD risk, including the rationale for treating early in life, genetic diagnosis, medications, and the need for family screening when genetic testing is positive. Elements of an FH implementation care plan include: integrating primary care clinicians, specialty clinicians, and physician extender roles; providing patient and clinician education; initiating guideline-recommended care, screening of first-degree relatives; allowing for process improvement; growing expertise/satisfaction within the primary care workforce; and including evaluation tools for outcomes related to establishing an FH diagnosis.

This project is a collaborative approach to identifying and reaching every patient in Geisinger with familial hypercholesterolemia. It aims to improve diagnostic evaluation rates of FH by transitioning the initial screening for FH into primary care and initiating guideline-based management for individuals prior to the onset of ASCVD. This paper presents the protocol for the Collaborative Approach to Reach Everyone with Familial Hypercholesterolemia (CARE-FH) study. 

## 2. Materials and Methods

### 2.1. Overview

The primary outcome of the CARE-FH study is to determine if clinicians who receive an implementation strategy package (defined as a collection of targeted implementation strategies) are more likely to increase diagnostic evaluation rates for FH and if this is acceptable and sustainable within current primary care practice [14]. Implementation science frameworks have been shown to increase the generalizability of research findings [15,16,17]; therefore, the results of this study will be aligned with the Conceptual Model of Implementation Research (CMIR) framework. The evidence-based interventions are derived from two clinical practice guidelines: 2018 American Heart Association and American College of Cardiology (AHA/ACC) Cholesterol Guidelines and the 2018 *JACC* Genetic Testing Statement [1,18]. The implementation strategies will be designed to deploy these evidence-based interventions into clinical practice. Outcomes in domains of implementation, service, and health will be sought. Generalizability to other health care systems will be an additional key goal [19]. CARE-FH is registered with ClinicalTrials.gov (accessed on 8 March 2022), number NCT05284513.

The initial phase of the grant (R61 National Institutes of Health (NIH) mechanism) will focus on trial design, including the development of implementation strategies to deploy the evidence-based intervention. The implementation phase (R33 NIH mechanism) will study the intervention, using a stepped-wedge design, and analyze data on FH diagnostic evaluation rates, and implementation, service, and health outcomes (Figure 1). Practice randomization strategies will be used as part of the stepped wedge design and rollout.

### 2.2. FH Diagnostic Evaluation Program

This program for FH care is based on the current paradigm for notification regarding actionable genetic variants in MyCode Community Health Initiative (MyCode) a research program that links exome sequence data with electronic health record (EHR) data and returns pathogenic variants in clinically actionable genes to patient-participants (Figure 2) [13,20,21,22,23,24,25]. Evaluation is triggered by the notification of the patient and primary care clinician of an actionable variant. In CARE-FH, there will be four possible triggers: the presence of an FH variant from MyCode, cascade screening of family members identified in the MyCode program, identification of patients requiring an FH workup through applications of FH screening algorithms of EHR data, or presence of an LDL-C ≥ 160 mg/dL in a child. Notification will lead to scheduling a medical appointment to complete the FH diagnostic evaluation. Successful completion of the FH diagnostic evaluation, the primary outcome of this study, will include evidence the clinician has completed evidence-based FH diagnostic evaluation and management goals. The goals are defined as completing one of the following:-Used FH clinic note to document care-Added FH diagnosis on the problem list or used the Dutch Lipid Clinic Network score (DLCN) tool to exclude FH diagnosis-Used the FH smart-set (i.e., ordered a genetic test for FH)-Made a referral to the lipid clinic [12]-Initiate evidence-based lipid lowering medications

A patient will be considered to have FH if they have a positive genetic test for FH or have a DLCN > 8 and probable FH with a score of 5–8. Geisinger primary care sites are divided by geographic region (Central, Northeast, Western, or Geisinger Medical Center) and into several practice types. Adult-oriented primary care clinics are staffed by internists, family practitioners, and advanced practice professionals (physician assistants and nurse practitioners). Pediatric practices provide primary care and acute care at 22 clinics.

### 2.3. Potenital Implementation Strategies

Based on previous work [26], preliminary implementation strategies were developed for Aim 1 of this study (Table 1). These implementation strategies were mapped to the Expert Recommendations for Implementing Change (ERIC) compilation, a list of strategies generated by experts in implementation strategies, to improve their generalizability to future research studies [19]. Also, the implementation strategies were defined using the Proctor’s framework for specifying implementation strategies and these will be modified in Aim 1 of the study [27].

## 3. Specific Aim 1 (R61): Design a Clinical Trial to Assess Multi-Level Implementation Strategies for Improving FH Diagnosis in an Integrated Health System

### 3.1. Objectives and Work Plan by Team

#### 3.1.1. Implementation Science Team (ImpT)

The ImpT will meet bi-monthly to accomplish the objectives outlined below.

Identification of healthcare system level barriers.Tailor selected implementation strategies to meet the needs of the clinical implementation sites.Alpha testing of implementation strategy package into two preselected clinical implementation sites.Define a measurement of implementation outcomes.

Surveys and in-person contextual inquiries (defined as observations with interviews) with clinicians at community adult and pediatric practices will be conducted to understand barriers to the implementation of the proposed strategies. The implementation strategy package will be designed and reviewed in two deliberative engagement meetings with the Medical Science Team (MedT). The Informatics and Data Science Team (InfT) will design, build, test, and implement information technology (IT)-based strategies in partnership with the ImpT. The main outcome is the selection and design of the individual components of the implementation strategy package and definitions of implementation outcomes.

##### Survey

Prior to alpha-testing of selected implementation strategy package, Geisinger primary care clinicians will be asked to complete the 12-item validated survey, Acceptability of Implementation Measure, Implementation Appropriateness Measure, and the Feasibility of Intervention Measure [28], to assess readiness for adoption of the implementation strategy package. Descriptive analyses including means and standard deviations or median and inter-quartile ranges, depending on distribution, will be reported for each scale. Plots, including histograms and box plots, will be used to identify outliers. To examine trends across multi-level scales, each construct will be examined independently, as well as a composite adoption score. Scatter plots will be used to examine for any association between pairs of scales. Correlations between the various scales will be estimated using Pearson and Spearman rank-order correlation coefficients.

##### Contextual Inquiries

Human-centered design visual artifacts will be developed to synthesize and illustrate the current state of the process of FH identification at clinic sites. These artifacts may include service blueprints, journey maps, and/or experience maps as appropriate. These artifacts will serve as a baseline of the current workflow, clinician, and patient experience, and as a shared understanding to identify areas of opportunity to innovate and improve. As roll out will be by geographical region, (Central, Northeast, Western, and Geisinger Medical Center), covariates will be defined and summarized by region, individual clinic, and practice type (pediatric, internal medicine, family practice). Examples include: Cluster-level covariates such as the percent of the population meeting the definition of rural or underserved; Clinic-level covariates including size, clinician experience (including trainees); Clinician-level covariates such as demographics (age, sex, race), and clinician type.

##### Deliberative Engagement Meetings

Based on the findings of the survey and contextual inquiries, we will tailor the selected implementation strategies, using evidence-based techniques from human-centered design and implementation science. We will hold two deliberative engagement meetings with the MedT to develop and refine the multi-level implementation strategy package. One meeting will be held prior to the alpha test site roll-out; the second will further tailor the implementation strategy package to be used for the clinical trial (Aim 2).

#### 3.1.2. Medical Science Team (MedT)

The MedT will meet monthly to accomplish the objectives outlined below.

Partner with the InfT to revise content for EHR tools in the implementation strategy package and subsequent adaptations.Finalize FH care plan for adults and children.Finalize strategy for incorporation of genetics counselors and specialty referrals into a care plan.Finalize study timeline, including the schedule and sites for rolling out the implementation strategy package.Alpha test the implementation strategy package at one adult and one pediatric practice site.

Interviews performed by the ImpT with clinicians at adult and pediatric practices will be used to refine the structure for the rollout of the implementation strategies. Strategies to increase pediatric screening rates will be developed. The alpha test will occur at one adult and one pediatric clinic at the main hospital, staffed by a member of the MedT. All tools developed for the implementation strategy package will be tested, using principles from human-centered design. The alpha test will be further informed by interactions with end users to assess workflow as part of the human-centered design activities. The main outcome of the R61 phase of the study will be successful first rollouts.

#### 3.1.3. Informatics and Data Science Team (InfT)

The InfT will meet monthly to accomplish the objectives outlined below.

Partner with the MedT to develop content for building EHR tools for the implementation strategyProvide EHR support for the alpha test.Finalize the data analysis plan.Collect baseline outcomes data, including estimates of patient flow, for the clinical trial design.

The InfT will obtain the final study protocol and materials from the ImpT and MedT. These will then be embedded into Geisinger IT systems, with testing of the ability to present information (including patient flow) and extract data. Initial testing of EHR tools will occur in the EHR development environment. This utilizes an industry best practice for testing innovation and enhancements prior to full deployment, facilitates user interaction, allows feedback, and ensures the proposed interventions are integrated with clinician workflow. The primary outcome of Aim 1 for the ImpT will be the successful collection of study outcomes from the EHR to serve as baseline data for the usual care arm of the trial.

## 4. Specific Aim 2 (R33): Compare FH Diagnostic Evaluation Rates among Primary Care Clinicians Who Receive the Implementation Strategy Package versus Those Who Do Not

We will conduct a type 3-hybrid effectiveness-implementation trial using a stepped-wedge design to test the effectiveness of the implementation strategy package designed in the R61 phase of the project [29]. The rollout will occur by Geisinger geographic region: Central, West, Northeast, and Geisinger Medical Center. Clinics within each region will be randomized as to the order of receiving the implementation intervention. Data will be collected on the primary and secondary outcomes before and after the intervention to measure change. After each step, we will use an iterative review process to re-assess the fit of the multi-level implementation strategy package and make adaptations, such as repeat sessions for clinics with new trainees, as needed. This aim will examine implementation outcomes including adoption and penetration of an FH diagnosis program (Table 2). We hypothesize: That clinicians that receive the implementation strategy package will have an improved rate of diagnostic evaluation for FH compared to those in the usual care group.

### Data Collection and Analysis for Adoption and Penetration

All primary care clinics in the Geisinger system will be included in the study. Clinicians who have a patient who requires diagnostic evaluation for FH will receive an EHR-based notification. The clinician or designee will call the patient to discuss the next steps and schedule an appointment for an FH diagnostic evaluation (Figure 2). At the same time, adults, or parents of pediatric patients, will be notified by mail and telephone of the need for evaluation.

Data will be analyzed at the level of clinics, clinicians, and patients and stratified by the study phase. Bi-variate analyses will be used to assess differences in outcomes between the intervention and control periods. We will also follow the CONSORT 2010 [30] extension to stepped-wedge trials when reporting results. The percentages of FH diagnostic evaluations completed will be reported every six months. Follow-up will continue through the end of the study (48-months). Characteristics of clinicians and clinics will be summarized by exposure status to allow consideration of selection bias and lack of balance. FH diagnostic evaluation rate will be analyzed using a generalized linear mixed effects model [31,32], with completion of the FH diagnostic evaluation as a binary outcome, intervention, time, and their interaction as fixed-effects, cluster as random-effects, along with other covariates as predictors. The covariates will be selected by the advisory board based on previous evidence of the effect on FH diagnostic evaluation rates. A mixed effects model will be used to account for the hierarchical clustering structure of data (patients per clinician, clinicians per clinic). The model assumes that the intervention effect and time effects are common to all clusters, and that observations are equally correlated within clusters across time. In the primary analysis, adult and pediatric clinics will be analyzed separately however commonalities will be sought and, when appropriate, pediatric, and adult behavior will be compared. Of particular interest are differences in performance among adult and pediatric clinicians. Sample sizes were based on a power calculation considering a meaningful implementation strategy package as a 20% improvement in FH diagnostic evaluation rate and required a minimum of 10 clinics per region. Statistical analyses will be conducted using RStudio (Version 1.3.1093) [33]. *p*-values of less than 0.05 are considered statistically significant.

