### 6.1. Data Collection and Analysis for Service and Health Outcomes

#### 6.1.1. Timeliness

For measurements looking at the time to completion of tasks, key dates will be the date of first FH notification, date of the clinic visit, and dates of supporting patient contacts such as genetic counseling and lipid specialty appointments. Visits with genetic counselors will be used to assist with the tracking of genetic testing and cascade screening of relatives. An initial visit to a lipid specialist will be used to determine the time for statin initiation, if not done at the primary care visit. The 2018 AHA/ACC cholesterol guideline will be used to define evidence-based indications and goals related to statin initiation [1]. Timeliness outcomes will be analyzed using time-to-event models, including the Cox Proportional Hazard regression model.

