#### 6.1.2. Function

Data to be extracted from the FH Clinic Note and follow up assessments include the presence of a definite or probable FH diagnosis or used DLCN tool to exclude FH diagnosis, medication prescribing, medication-related side effects, lipid levels (to assess compliance with evidence-based care), genetic test ordering, return of genetic results, and initiation of cascade screening. We will use descriptive statistics and compare outcomes between intervention and control conditions every six months and with reference to the four steps.

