**Figure 2 jpm-12-00606-f002:**
[figure not shown]
FH Diagnostic Evaluation Program. ASCVD, atherosclerosis cardiovascular disease; DLCN, Dutch Lipid Clinic Network score; FH, Familial hypercholesterolemia; Clinics will move from usual care to deployment of implementation strategy package during the stepped-wedge design.

**Table 1 jpm-12-00606-t001:** Potential implementation strategy package.

Name of Strategy *	Study Specific Definition	Actor	Action	Action Target
Develop and implement tools for quality monitoring	EHR tools to order labs, record results, and document FH care	ImpT, MedT, and InfT	Use EHR to record, order, and prescribe FH Care	Service and health outcomes
Develop educational materials	Education regarding guidelines for identification and treatment of FH	MedT and InfT	Create a CME course for clinicians about FH. Explore clinician workflow and educational needs to design novel focused educational interventions integrated within clinical workflows to support evidence-based care	MedT ready to train clinicians on FH
Conduct educational outreach visits	CME educational material for FH that is presented to each clinic	MedT and clinicians	Attend CME course on FH	Improve knowledge about FH
Intervene with patients to enhance uptake and adherence	Reach out directly to patients to recommend screening for FH	Clinicians and ImpT	Letter sent to the patient. Clinician schedules patient for appointment.	Patients diagnosed with FH from those at-risk
Identify and prepare champions	Clinical lipid champions	MedT	Identify and train lipid champions	Improved performance of study metrics, reduced costs
Stage FH care delivery model scale up	Develop the timeline for the stepped-wedge rollout to primary care	Leadership team	Notify practices of roll out and schedule education	Begin the trial
Audit and provide feedback	Provide aggregate level feedback to clinics on diagnosing FH	MedT, InfT, and clinical leadership	Report back to clinicians’ aggregate level data	Improve effectiveness of the FH Diagnosis Program
Advisory board review	Clinical trial protocol	Advisory Board	Provide feedback on the clinical trial regarding protocol, generalizability and ethical issues	Protocol revision based on feedback

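### Pooled period comparisons and timeliness Cox models name no calendar-time or clinic term in a stepped wedge; the timeliness origin and the statin start date also need fixing

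*Protocol article*

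**What the plan says.** All references are to the protocol article.

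- **Aim 2, Data Collection and Analysis for Adoption and Penetration:** "Bi-variate analyses will be used to assess differences in outcomes between the intervention and control periods". The same paragraph sets significance at p below 0.05. For the FH diagnostic evaluation rate it specifies a generalized linear mixed model with "intervention, time, and their interaction as fixed-effects, cluster as random-effects, along with other covariates as predictors". It then adds: "A mixed effects model will be used to account for the hierarchical clustering structure of data (patients per clinician, clinicians per clinic"). It does not say which outcomes beyond the primary this sentence covers.
- **Section 6 (Aim 4):** the hypothesis is comparative. Service and exploratory health outcomes are expected to be reached more often once the package is deployed at the clinic.
- **Section 6.1.1, Timeliness:** "Timeliness outcomes will be analyzed using time-to-event models, including the Cox Proportional Hazard regression model". The listed "key dates will be the date of first FH notification", then the clinic visit and supporting contacts. No date is named as time zero. "An initial visit to a lipid specialist will be used to determine the time for statin initiation" when a statin was not started at the primary care visit.
- **Section 6.1.2, Function:** the plan is to use descriptive statistics and "compare outcomes between intervention and control conditions every six months and with reference to the four steps".
- **Table 1** lists, as one potential package strategy: "Letter sent to the patient. Clinician schedules patient for appointment".

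**The concern.** In a stepped wedge every clinic contributes control data first and intervention data afterwards. Pooling all control observations against all intervention observations therefore compares earlier with later calendar time as well as usual care with the package. Any drift in lipid testing, statin use or FH awareness over the 48 months enters the contrast. Patients in the same clinic are also correlated, and a bivariate test treats them as independent.

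The plan handles both problems for the primary outcome but does not clearly carry the solution to the others. At stake is the credibility of the secondary and Aim 4 comparisons.

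Timeliness raises two further questions. A time-to-event comparison needs a start date that is defined alike in both conditions. The endpoint date also has to be the date on which the event happened.

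**Working it through.** **The plan's own figure.** The article gives no number for these analyses. Its one design figure, at least 10 clinics per region for a 20% improvement, concerns the primary outcome. It cannot be reproduced, because baseline rate, power, ICC and patients per clinic are not given. It serves below only to set an illustrative size of 4 x 10 = 40 clinics.

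**Calendar imbalance.** Four steps are stated (sections 5.1.1 and 6.1.2). Five equal periods, one step per period and equal cell sizes are assumptions. The group that crosses over after period k is in control for periods 1 to k.

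- Control cells: 1 + (1+2) + (1+2+3) + (1+2+3+4) = 20 over 10 cells, mean period 2.0.
- Intervention cells: (2+3+4+5) + (3+4+5) + (4+5) + 5 = 40 over 10 cells, mean period 4.0.
- Bias of a pooled difference under linear drift = (4.0 - 2.0) x change per period = 2 x change per period.

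A rise of 1, 2 or 3 points per period thus gives a spurious gain of 2, 4 or 6 points. A fall gives a spurious loss of the same size.

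**Error rates with no intervention effect.** Simulation, 2,000 runs per scenario. Assumed, not in the article: 40 clinics, 10 per step; 10 or 20 patients per clinic-period; baseline 20%; ICC 0.02, 0.05 or 0.10. Nominal two-sided level 5%. Ranges run over the six combinations of cluster size and ICC.

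| Rise per period | Pooled difference | Pooled test | Stratified by period, clinics ignored | Clinic and period effects |
|---|---|---|---|---|
| 0 points | about 0 | 7-25% | 11-36% | 4-5% |
| 1 point | about 2 points | 21-42% | 10-36% | 4-6% |
| 2 points | about 4 points | 54-82% | 10-36% | 5-6% |
| 3 points | about 6 points | 79-98% | 9-32% | 5% |

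The Monte Carlo standard error at 5% is sqrt(0.05 x 0.95 / 2000), about 0.5 points. The first row isolates clustering. Stratifying by period removes the bias but not the excess error, so a comparison within six-month windows still needs clinic effects.

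**Timeliness origin.** Three places bear on whether control-period patients have a notification date:

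- Section 2.2 describes MyCode variant notification as existing practice.
- The Aim 2 data collection text describes the EHR notice with all primary care clinics included and does not limit it to the intervention period. Patients are to be told by mail and telephone at the same time.
- Table 1 lists the patient letter and scheduling as a potential package strategy.

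These do not settle whether control-period patients are notified in the same way. If they are not, the two conditions have no common time zero if the clock starts at notification.

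**Statin date.** Read literally, section 6.1.1 uses the first lipid-specialist visit whenever the statin was not started at the primary care visit. A start at another contact before that visit is then dated late, and a start in a patient who never sees the specialist is missed. Referral to the lipid clinic is one of the actions that count toward the primary outcome, so this error could differ between conditions. Section 6.1.2 extracts medication prescribing, and Table 2 gives EHR and administrative data as the timeliness source, so a direct date should be available.

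**The case against.** The strongest reply is that this is a condensed article. Finalizing the data analysis plan is a deliverable of Aim 1 (section 3.1.3), and frailty terms, calendar strata and time zero are ordinary SAP content. The wording on time-to-event models is open-ended. The bivariate sentence stands in the Aim 2 section before the mixed model and can be read as a descriptive first step. The general mixed-model sentence may cover penetration.

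Much of this stands. The Cox point is about terms not named, not terms excluded. The bivariate sentence is different: it states a method for assessing differences between periods, beside a significance threshold, and does not call it descriptive.

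Four stronger readings are tempting, and the text does not support them.

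- *That Aim 4 function outcomes ignore calendar time.* Section 6.1.2 compares every six months and by step, which partly handles calendar time. Only clustering is left open.
- *That notification belongs to the package, so package mechanics would show as faster care.* Table 1 places only the patient letter and scheduling there, as a potential strategy. Notification is not shown to be confined to the intervention period, and no direction of bias can be derived.
- *That secular change must look like benefit.* This needs a rising trend; a falling one would hide benefit.
- *That the six-monthly comparisons create a large multiplicity problem.* Section 6.1.2 speaks of descriptive statistics and states no series of tests.

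**Conclusion.** The concern holds for the pooled bivariate comparison of periods and, as an unstated adjustment, for the timeliness Cox models. The pooled contrast carries about two periods of any secular change, in either direction, under the assumed 4-step, 5-period layout with linear drift. Its p-values also ignore clinics: with no trend at all, the nominal 5% becomes 7-25% over the assumed inputs. The actual layout, ICC, cluster sizes and trend are not given, so these figures show plausible size and do not predict this trial's results. They come from a binary outcome and do not measure the error of the Cox models.

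The six-monthly, by-step function comparison is exposed to clustering only, and only if it is used for inference. The timeliness origin is unclear for control-period patients, with bias of unknown direction. The statin rule, read literally, misdates or misses some starts. The primary mixed model is not affected.

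**What to change.** - Analyse each comparative secondary and Aim 4 outcome with calendar period and intervention as fixed terms and clinic random effects. State which outcomes the general mixed-model sentence covers.
- For Cox models, adjust for or stratify by calendar period, treat clinic exposure as time-varying so that a patient whose clinic crosses over is classified correctly, and use a clinic frailty or a clinic-robust variance.
- Present bivariate and six-monthly tables descriptively, without p-values.
- Define a timeliness origin observable in both conditions, such as the date a trigger is first met under the same EHR query. State whether control-period patients are notified. Entry through cascade screening needs its own rule, because starting cascade screening is itself an Aim 4 outcome.
- For the analysis, date statin initiation by the first EHR order or prescription, wherever it was written.

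The cost is analysis wording and programming on data already planned, and somewhat wider intervals.
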